## Abstract

Physical inactivity, maladaptive exercise motives, and body image concerns are highly prevalent among young adult women and are associated with reduced psychological well-being and increased risk for disordered eating. Although previous interventions have addressed physical activity or body image separately, few have simultaneously targeted motivational quality and body-related perceptions within an integrated theoretical framework. This study protocol describes a randomized controlled trial designed to evaluate the effectiveness of a psychoeducational intervention based on Self-Determination Theory and using functionality-oriented body image strategies. The aim is to enhance autonomous motivation for exercise and improve psychological well-being among female university students in Health Sciences. Participants aged 18–25 years will be randomly allocated (1:1) to an experimental group or a wait-list control group following baseline assessment. Outcome measures will be collected at baseline (T0), post-intervention (T1), and six-month follow-up (T2). The intervention consists of six face-to-face group sessions that include autonomy-supportive strategies, competence-building activities, and functionality-based body image content emphasizing body capabilities rather than appearance. The primary outcome is autonomous motivation for exercise, assessed using the Behavioral Regulation in Exercise Questionnaire-3 and operationalized through the Relative Autonomy Index at six-month follow-up. Secondary outcomes include satisfaction and frustration of basic psychological needs, physical activity levels, positive body image, and risk of eating disorders. Data will be analyzed using mixed model for repeated measures under an intention-to-treat framework to account for repeated measures and missing data. Mediation analyses will examine whether changes in autonomous motivation explain the effects of the intervention on physical activity, positive body image, and eating disorder risk. This study will provide evidence on the effectiveness of an integrated, theory-based intervention targeting motivation and body image in young adult women. The trial is registered at ClinicalTrials.gov (Identifier: NCT07506343).

## Introduction

The university period represents a developmental stage characterized by increased autonomy, profound lifestyle changes, and heightened vulnerability to health‑related behavior disruptions. Insufficient physical activity (PA) and high sedentary time remain highly prevalent among university students worldwide [1]. Global surveillance data show a persistent gender gap in PA participation: women report markedly higher inactivity rates (31.7%) compared to men (23.4%), reaching up to 42.3% in high‑income Western countries [2]. These patterns are concerning, as physical inactivity tends to increase during early adulthood and is associated with adverse long‑term physical and psychological outcomes [3,4].

Concurrently, the university stage coincides with elevated susceptibility to body dissatisfaction, internalization of appearance ideals, and risk factors for eating disorders (ED). Recent epidemiological data in Spain report a point prevalence of 7.8% for EDs, with young women representing the group at highest risk [5]. Body dissatisfaction, exposure to unrealistic appearance ideals, and the pervasive influence of social media amplify this vulnerability [6,7]. Importantly, PA in this population can become maladaptive when driven by controlled motives such as guilt, social pressure, or appearance management [8,9]. Understanding not only whether, but why, young women engage in PA is therefore essential to prevent maladaptive patterns and promote sustained well‑being.

Self-Determination Theory (SDT) provides a comprehensive framework for understanding motivational processes associated with PA engagement and psychological health [10,11]. SDT differentiates autonomous motivation, rooted in personal values, interest, and volition, from controlled motivation, which arises from internal or external pressures. Autonomous motivation predicts sustained PA, greater psychological well-being, and healthier body attitudes, whereas controlled motivation is associated with poorer adherence and emotional distress [12,13]. Central to SDT is the satisfaction of the basic psychological needs for autonomy, competence, and relatedness; meta-analytic evidence shows that interventions supporting these needs improve motivational quality and promote health-related behavioral regulation [14,15]. Recent analyses further demonstrate that combining multiple need-supportive strategies, autonomy-supportive communication, structure, and relational support produces the strongest effects on motivation and PA adherence [14].

In parallel, increasing evidence emphasizes the relevance of positive body image, particularly functionality appreciation, the recognition of what the body can do rather than how it looks, as a protective factor for young women [16,17]. Functionality-focused interventions have shown significant improvements in body appreciation and reductions in ED risk indicators among adolescents and young women [16,18]. This approach aligns conceptually with SDT, as it shifts individuals toward intrinsically rewarding, self-endorsed reasons for engaging in PA. Integrating functionality appreciation into motivational interventions may reduce maladaptive appearance-based motives while simultaneously reinforcing autonomous regulation and intrinsic reasons for engaging in PA.

Despite advances in both research areas, notable gaps remain. Few university‑based interventions jointly target (a) the quality of motivation for PA and (b) body image or ED‑risk factors within a unified SDT‑informed framework. Existing interventions often address these components separately, limiting their effectiveness. Moreover, evidence from Mediterranean populations is scarce, and many studies lack follow-up assessments or include only short-term evaluations, restricting conclusions regarding the sustainability of observed changes [15,19].

To address these gaps, the present study describes a randomized controlled trial evaluating a psychoeducational intervention designed to enhance autonomous motivation for PA and promote positive body image among female Health Sciences students. Grounded in SDT and enriched with functionality-focused components, the intervention targets theoretically central mechanisms, basic psychological need satisfaction and autonomous regulation, to support sustainable PA engagement and reduce vulnerability to ED-related risk factors. By intervening in a high-risk developmental period and focusing on future health professionals, this trial holds potential not only for improving individual well-being but also for fostering autonomy-supportive communication styles that may influence future clinical practice.

Based on the theoretical framework, existing empirical evidence, and the identified gaps in the literature, the present study proposes the following hypotheses:

*Primary hypothesis*

H1. The intervention will significantly increase autonomous PA motivation (BREQ-3; Relative Autonomy Index) at post-intervention (T1) and follow-up (T2).

*Secondary hypotheses*

H2. Participants will report higher basic psychological need satisfaction (autonomy, competence, and relatedness; BPNSFS) at post-intervention (T1) and follow-up (T2).H3. PA levels (IPAQ-SF) will increase significantly at T1 and T2.H4. Participants will show significant improvements in positive body image (BAS-2).H5. Eating disorder risk (EAT-26) will be significantly reduced.

*Mediation hypothesis (key mechanism)*

H6. Changes in autonomous motivation will mediate the intervention’s effect on PA levels and health-related psychological outcomes.

## Materials and methods

This study protocol follows the SPIRIT (Standard Protocol Items: Recommendations for Interventional Trials) 2025 guidelines (see supplementary material S1 File) [20]. The intervention is described in accordance with the Template for Intervention Description and Replication checklist (see supplementary material S2 File) [21], which complements SPIRIT 2025 recommendations for reporting interventions.

### Study design

This study design is a randomized controlled trial (RCT), comprising an experimental group and a control group. Three assessment time points are planned: baseline (T0), immediate post-intervention (T1), and a six-month follow-up after completion of the intervention (T2). This design will allow examination of the effectiveness of a psychoeducational intervention grounded in Self-Determination Theory [10], aimed at fostering more autonomous motivation toward physical activity among female university students.

The study will be conducted at Universidad Francisco de Vitoria (Madrid, Spain), in facilities designated for face-to-face group workshops. The total duration of the project is estimated at twelve months, including preparation, recruitment, intervention implementation, data analysis phases, and dissemination of results.

### Participants’ eligibility

The target population will consist of female university students aged 18–25 years, enrolled in Health Sciences degree programs. This age range was selected because it corresponds to a developmental stage characterized by significant changes in health-related behaviors and increased psychological vulnerability, thus highlighting the relevance of preventive interventions within the university context [4,22].

The focus on Health Sciences students is particularly relevant, as they are future health professionals. Research suggests a ‘motivational spill-over’ effect, where fostering autonomous regulation in their own health behaviors (like PA) can later improve their professional ability to support their patients’ autonomy [12].

Participants must meet all of the following criteria:

Female sexAged between 18 and 25 yearsEnrolled in a Health Sciences degree programProvide written informed consent indicating voluntary participation

Participants will be excluded if they:

Report a current or previous diagnosis of an eating disorder

### Recruitment

Participant recruitment will be conducted centrally by the university to ensure compliance with institutional data protection regulations. This communication will include standardized information about the study, prepared and authorized by the Ethics Committee, as well as a link to the online registration form. Students who are interested may voluntarily access the link, review detailed information about the study, and complete the eligibility screening. Because all eligible students receive a personal email invitation (a census of the eligible population), no probability sub-sampling of the invitation frame is applied. To characterize and address volunteer self-selection at the response stage, the overall and stratum-specific response rate will be reported, respondents will be compared with the full invited eligible population on available administrative characteristics (degree program and year of study), and a post-stratification / inverse-probability-of-response weighting sensitivity analysis will be conducted (see supplementary material S3 File). Only those who self‑enroll and meet the inclusion criteria will be asked to provide written informed consent prior to participation. At no stage during this initial outreach will the research team access personal data of non‑interested students, thereby ensuring full adherence to data protection guidelines and safeguarding confidentiality throughout the recruitment process. No financial compensation will be provided for participation. However, participants will be offered access to a structured psychoeducational program and, in the case of the control group, delayed access to the full intervention after completion of the study. This approach was selected to balance ethical considerations and feasibility within the academic context.

### Withdrawals

Participants will be free to withdraw from the study at any time without academic or personal consequences. Participants will also be withdrawn if a current or previous diagnosis of an eating disorder is identified after the initial screening phase. In such cases, participants will be debriefed and referred to specialized university health services. All withdrawals will be fully documented, including the reason for withdrawal and the time point at which it occurs. Data analyses will be conducted according to the intention-to-treat principle, incorporating all available data up to the time of withdrawal in order to preserve the benefits of randomization and minimize attrition bias.

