### Randomization, blinding, and allocation

Following baseline assessment, participants will be randomly allocated to either the experimental or the control group in a 1:1 ratio. The allocation sequence will be generated in R using the *blockrand* package by an independent researcher not involved in participant recruitment, intervention delivery or outcome assessment, with a random seed kept confidential until recruitment is complete.

Block randomization will be used, with permuted blocks of variable size (4, 8, and 12) and 1:1 allocation within each block, without stratification given the homogeneity of the target population in age and academic context. Using variable block sizes that are not disclosed to enrolling staff preserves allocation concealment by preventing prediction of forthcoming assignments, while ensuring balanced group sizes throughout recruitment and minimizing selection bias.

Recruiting and enrolling staff remain masked to the allocation sequence and to the (variable) block sizes throughout the trial. As a post-hoc verification of the absence of allocation selection bias, a Berger–Exner test will be applied to check for any association between the allocation sequence and baseline prognostic characteristics.

Due to the nature of the psychoeducational intervention, blinding of participants and intervention providers (facilitators) will not be feasible. Outcome data will be collected using self-administered standardized questionnaires, minimizing assessor-related bias.

Researchers involved in data management and statistical analysis will remain blinded to group allocation until the primary analyses are completed. Data will be coded using anonymized group identifiers to ensure concealment during analysis.

This approach ensures appropriate separation between sequence generation, allocation concealment, and blinding procedures, in accordance with established guidelines for randomized controlled trials.

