#### Experimental intervention.

Participants assigned to the experimental group will take part in a face-to-face psychoeducational program consisting of six 60-minute group workshops, conducted in small groups of up to 15 participants. Each participant remains in the same delivery subgroup across the six sessions. This format facilitates social interaction and the creation of a need-supportive climate, factors identified as relevant in interventions based on Self-Determination Theory (SDT). Sessions are facilitated by trained professionals with experience in exercise science and psychonutrition, who receive standardized training prior to intervention delivery to ensure consistency across groups. Facilitators complete standardized training covering SDT principles, functionality‑based body image strategies, session structure, and fidelity procedures. The intervention includes structured presentation slides, participant worksheets, guided experiential activities, and reflective exercises. Detailed intervention materials are available from the authors upon reasonable request. Minor contextual adaptations (e.g., examples or wording adjustments) may be made, but core intervention components remain unchanged. The intervention will be delivered following a standardized manual based on established SDT techniques, including autonomy support, structure, and involvement [13,14], as summarized in Table 1.

**Table 1 pone.0355374.t001:** Structure, objectives, and Basic Psychological Needs-Supportive Strategies targeted in the intervention workshops.

Workshop	Primary focus	Need-Supportive Strategies (SDT-based)	Basic Psychological Needs targeted
1	Awareness of motivational quality toward PA	Providing a meaningful rationale: explaining the “why” behind PA engagement.	Autonomy
2	Personal values and autonomously chosen goals	Autonomy support: promoting the internalization of PA goals based on personal interests.	Autonomy & Competence
3	Perceived competence and flexible planning	Structure: providing clear guidance, mastery-oriented feedback, and skill-building for PA.	Autonomy & Competence
4	Positive body image from a functionality-oriented perspective	Acknowledging perspectives: validating participants’ feelings and fostering intrinsic values.	Autonomy & Relatedness
5	Social support and supportive relational climate	Involvement: fostering a warm, supportive, and non-judgmental climate for PA.	Relatedness

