### Wait-list control condition

Participants assigned to the control group will remain on the wait-list during the intervention and follow-up periods and will not receive any specific intervention. To ensure intervention equity, they will be offered access to the full program upon completion of the T2 assessment.

Participants in both groups will be allowed to continue their usual activities and access external health-related services (e.g., psychological support, personal training, or dietary counseling) throughout the study period. To monitor potential sources of contamination, participants will be asked to report any engagement in such services during the study.

These data will be recorded and considered in the interpretation of the findings. If deemed necessary, additional sensitivity analyses will be conducted to explore the potential impact of external interventions on the study outcomes.

All protocol deviations, including non-adherence to the intervention or engagement in external programs, will be documented and reported following established guidelines for randomized controlled trials.

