No physical risks are anticipated as a result of participation in the intervention. However, given the inclusion of sensitive questionnaires related to body image and eating disorder risk, a participant well-being protocol will be implemented. This protocol includes referral to university psychological support services if risk indicators are identified. No financial compensation will be provided; however, equity will be ensured by offering participants in the control group full access to the intervention program after completion of the follow-up assessment.

The wait-list control design was selected for both methodological and ethical reasons. From an ethical perspective, it ensures that all participants will eventually have access to the intervention, which is particularly relevant in university-based preventive programs targeting body image and motivational processes. Methodologically, this design may enhance participant retention and reduce attrition bias. Moreover, the use of a wait-list rather than an active or minimal-intervention control condition allows clearer detection of intervention-specific effects on perceived autonomy support and motivational regulation.

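### Randomised participants are withdrawn, with data used only up to that point, if an eating-disorder diagnosis is identified after screening; this contradicts the claim of intention-to-treat that preserves randomisation

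*Protocol article*

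**What the plan says.** Eligibility (Participants' eligibility) rests on self-report. Students are excluded if they "Report a current or previous diagnosis of an eating disorder", and this is checked in the online registration form before consent (Recruitment). Baseline comes next, and then allocation: "Following baseline assessment, participants will be randomly allocated to either the experimental or the control group in a 1:1 ratio".

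The Withdrawals section adds a later rule: "Participants will also be withdrawn if a current or previous diagnosis of an eating disorder is identified after the initial screening phase". It sets no end date. The same paragraph describes the analysis as intention-to-treat, "incorporating all available data up to the time of withdrawal in order to preserve the benefits of randomization and minimize attrition bias".

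Under Statistical analysis, the primary MMRM models the post-randomisation assessments, with the baseline value as a covariate. The primary endpoint is the group difference at six months. Validity rests on data being missing at random.

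The arms differ in contact. The experimental arm has "six 60-minute group workshops, conducted in small groups of up to 15 participants", and "Sessions are facilitated by trained professionals with experience in exercise science and psychonutrition". Controls "will remain on the wait-list during the intervention and follow-up periods and will not receive any specific intervention". Both arms complete the questionnaires at all three time points.

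**The concern.** Intention-to-treat means following and analysing everyone who was randomised. Here the study itself removes some randomised participants and stops using their data from that moment. The missing data come from a conduct rule, not from the participant's choice, and the trigger is clinically close to what EAT-26 and BAS-2 measure.

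Such an exclusion is harmless if it strikes both arms equally, or if diagnosis status says nothing about the outcome beyond the baseline score. The plan secures neither. If more cases surfaced in the experimental arm and those removed had worse eating attitudes, the remaining experimental participants would look better on EAT-26 and BAS-2 than the randomised group did. An analysis plan can probe that bias, but it cannot recover T1 and T2 answers that were never collected.

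**Working it through.** **Step 1: when the rule bites.** By the Study and participant timeline, recruitment and screening run October to December 2026, baseline is January 2027, T1 is complete by March 2027, and T2 is in September 2027. Randomisation follows baseline. The rule therefore covers a stretch before randomisation (screening to January) and a longer one after it (January to September).

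**Step 2: what the model does with a withdrawn participant.**
- Withdrawn before randomisation: no effect on the comparison.
- Withdrawn after randomisation, before T1: only the baseline value exists. It is a covariate, so there is no outcome row and the participant is not in the MMRM.
- Withdrawn between T1 and T2: one row, with no value at the primary endpoint.

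The second and third cases do not fit the claim that randomisation is preserved.

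**Step 3: possible size.** The plan gives no figure for these withdrawals, so there is none to reproduce. Two of its numbers are used: the target of 196, giving 196/2 = 98 per arm, and the background point prevalence of 7.8% (Introduction) as the upper end of a range. Everything else is assumed:
- π, the share of randomised participants with an undisclosed or new diagnosis: 2% to 7.8%
- Δ, the mean difference between diagnosed and other participants: 0.5 to 1.5 SD
- dE and dC, the shares of those cases identified and withdrawn in the experimental and control arms

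After withdrawal, the diagnosed share remaining in an arm is π(1−d)/(1−πd). The bias in the arm difference is

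Δ × [π(1−dE)/(1−π·dE) − π(1−dC)/(1−π·dC)].

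At 80% versus 20% identified:
- π = 2%, Δ = 0.5: 0.5 × [0.004/0.984 − 0.016/0.996] = 0.5 × (0.00407 − 0.01606) = −0.006 SD
- π = 7.8%, Δ = 1.5: 1.5 × [0.0156/0.9376 − 0.0624/0.9844] = 1.5 × (0.01664 − 0.06339) = −0.070 SD

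Absolute bias in SD, before baseline adjustment:

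| Identified, experimental vs control | π 2%, Δ 0.5 | π 5%, Δ 1.0 | π 7.8%, Δ 1.5 |
|---|---|---|---|
| 50% vs 50% | 0 | 0 | 0 |
| 50% vs 10% | 0.004 | 0.020 | 0.045 |
| 80% vs 20% | 0.006 | 0.030 | 0.070 |
| 100% vs 0% | 0.010 | 0.050 | 0.117 |

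**Step 4: head count at 80% versus 20%.** Experimental: 98 × 0.02 × 0.8 = 1.6 to 98 × 0.078 × 0.8 = 6.1. Control: 98 × 0.02 × 0.2 = 0.4 to 98 × 0.078 × 0.2 = 1.5.

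**Step 5: baseline adjustment.** If the gap Δ is already present at baseline and the baseline-to-follow-up correlation is 0.6 (an assumption), a fraction 1 − 0.6 = 0.4 of the bias remains. At 80% versus 20% that is 0.4 × 0.006 = 0.002 to 0.4 × 0.070 = 0.028 SD.

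**Step 6: if outcomes are still collected.** With T1 and T2 data from every consenting randomised participant, this source of bias is zero whatever the identification rates.

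**The case against.** The strongest objection concerns imbalance. A reader might infer from the unequal contact that withdrawals will fall mainly on the experimental arm. The documents do not say so. They do not state how a diagnosis would be identified, the trigger is a diagnosis rather than a remark in a session, and nothing asks facilitators to take a history. The routes that are described apply to both arms. All participants complete EAT-26 and report external services such as psychological support, and the well-being procedure is tied to the questionnaires: "This protocol includes referral to university psychological support services if risk indicators are identified". The baseline EAT-26 comes before allocation, so some cases would be found while withdrawal is still harmless. All of this stands. Imbalance is possible, not established.

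A reader might also infer that the bias could use up 25% to 38% of the treatment effect: 5% × 1.5 SD = 0.075 SD, and 0.075/0.30 = 25%, 0.075/0.20 = 38%. That is not supported. It takes every case as identified in one arm and none in the other, ignores baseline adjustment, and divides a shift assumed for EAT-26 by effect sizes that Sample size sets for the primary contrast in relative autonomy. The 1.5 SD gap has no source, and the rule also covers past diagnoses, including recovered participants. Direction is not certain either: if those removed would have responded more than others, their removal would understate benefit.

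Finally, the article has all withdrawals documented with reason and timing, and analyses for data not missing at random may be in the SAP, which is not shown. The absence of such analyses is therefore no part of this point. What survives is the contradiction within Withdrawals and the loss of data that no later analysis can restore.

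**Conclusion.** The point holds as a contradiction between a conduct rule and the intention-to-treat claim beside it. Randomised participants can be removed by the study for a reason related to EAT-26 and BAS-2, and the MMRM then has no outcome from them, or no six-month outcome.

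The likely size is small. Under the assumptions shown (2% to 7.8% affected, 0.5 to 1.5 SD apart, 80% versus 20% identified) the bias is about 0.006 to 0.07 SD before baseline adjustment, and about 0.002 to 0.03 SD after it if the correlation is 0.6. It is zero if identification is equal in both arms. It bears mainly on EAT-26 and BAS-2. No figure was derived for the relative autonomy index, where the bias is probably small. The change should be made because it is cheap before recruitment begins and uncollected data cannot be recovered.

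**What to change.** Reconcile the withdrawal rule with the intention-to-treat statement by separating the end of intervention participation from the end of outcome collection.

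- Keep every randomised participant who does not withdraw consent for data in the T1 and T2 questionnaires and in the intention-to-treat analysis.
- Report diagnoses identified after screening as protocol deviations, by arm and by timing relative to randomisation.
- Exclude these participants only in a sensitivity analysis.

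Whether such a participant continues the workshops or is referred is a clinical matter for the investigators and is not addressed here.

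**Cost.** The protocol, consent and ethics wording must change. The questionnaires are already digital and self-administered, so little is added in conduct. There are two downsides: a few ineligible participants stay in the intention-to-treat set, and continuing sensitive questionnaires in people with a diagnosis needs explicit ethics approval and consent wording.
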